## Abstract

**Introduction::**

In South Korea, the prevalence of obesity has continuously increased over the last decade, and the burden of social and economic costs has also increased immensely. The purpose of this study is to investigate the clinical characteristics and current status of patients receiving herbal medicine (HM) treatment for weight loss in Korean medicine (KM) by constructing a multi-institutional prospective registry.

**Methods and analysis::**

This is a prospective, observational, multi-center registry, including patients visiting the KM clinics in South Korea for weight loss. This study will collaborate with 15 KM clinics and recruit patients into the registry between October 2021 and October 2022. The study population will include patients visiting the KM clinics for weight loss. A total of 1000 eligible patients visiting the KM clinics for weight loss who decide to undergo HM treatment will be enrolled in the registry. After enrollment, we will collect the individual characteristics of each patient, such as body mass index, body composition test, liver and kidney function tests, and information on prescribed HM. We will also record the adverse events at each visit.

**Discussion::**

This study is the first prospective, multicenter registry of HM for weight loss in KM clinics. The results of this registry may show the current status of patients who receive HM treatments for weight loss and provide evidence for reasonable decision-making on KM healthcare policy for obese patients in the future.

## Introduction

1

Obesity is a major risk factor of various diseases, such as cardiovascular diseases and metabolic diseases. The prevalence of obesity and overweight has been increasing gradually over the past decades. Consequently, the burden of social and economic costs has also been increasing immensely. In South Korea, the prevalence of obesity continuously increased from 29.7% in 2009 to 35.7% in 2018 in the total population.^[1]^ The total social and economic losses for obesity in Korea was 11.5 trillion KRW (10 billion USD) in 2016, which represents 0.7% of the Korean gross domestic product, and approximately 50% of the costs were medical expenses.^[2]^ With the increase in obese population, attempts to lose weight have also been continuously increasing with various weight control methods, such as regular physical activities, diet control, such as calorie restriction, and frequent weight monitoring.^[3]^ However, even if weight loss is achieved, its long-term results are generally poor and sustaining reduced weight can be difficult with lifestyle changes alone, and additional medical therapies may be needed.^[4]^ Among the weight control methods, herbal medicine (HM) is one of the most effective strategies in the Korean population.^[5,6]^

Korean medicine (KM) is recognized as the double axis of health care system of South Korea along with conventional western medicine. Supportive evidence has demonstrated the safety and effectiveness of HM for obesity compared with conventional medicine.^[7–11]^ However, it is also reported that some herbal formulas are associated with several adverse events (AEs),^[12,13]^ and in some cases, the government has imposed restrictions on the use of certain medicines because of safety concerns.^[14]^ In Korea, because of the low insurance coverage for KM obesity treatments, including prescribed HM, information, such as the prescribed medication and its AEs in real clinical practice of KM treatment for obesity are scarce. As part of the real clinical practice of KM treatment for obesity, many studies on KM registry are currently being attempted in KM.^[15–18]^ This registry study was designed to understand the characteristics of KM weight loss treatment, which is commonly used in Korea, centered on primary medical institutions for the first time in the KM field.

The purpose of this study is to investigate the clinical characteristics and current status of individuals who receive HM for weight loss in KM by constructing multi-institutional prospective registry. Overall, the aims of this registry are to:

(1)investigate the clinical characteristics and current status of treatment for weight loss;(2)evaluate the safety of various HMs for weight loss, based on nationwide registry outcome collecting process.

## Participants and methods

2

### Study design/setting

2.1

This is a prospective observational multi-center study enrolling patients undergoing KM weight loss treatment in Korea. We will recruit patients from the following 15 KM clinics: Bareun-mom S KM clinic (Hwaseong, Gyeonggi-do), Saeng-saesang KM clinic (Daejeon), Sangju Baraeun KM clinic (Sangju, Gyeongsang-do), Hwapyeong KM clinic (Incheon), Imom KM clinic (Changwon, Gyeongsang-do), Goeun KM clinic (Gunpo, Gyeonggi-do), Lee Seung Jin KM clinic (Namyangju, Gyeonggi-do), Onki KM clinic (Namyangju, Gyeonggi-do), Chunjin KM clinic (Boryeong, Chungcheon-do), Sogood KM clinic (Seongnam, Gyeonggi-do), Gyeongsan S KM clinic (Gyeongsan, Gyeongsang-do), Myoungjak KM clinic (Gunsan, Jeolla-do), Momandjang KM clinic (Gunpo, Gyeonggi-do), Kyurim KM clinic (Cheongju, Chungcheon-do), and Madimadi KM clinic (Yongin, Gyeonggi-do) between October 2021 and October 2022 (Fig. 1). Patients who provide informed consent to participate will receive KM weight loss treatment according to their individual characteristics without any intended intervention. At baseline (recruitment), comprehensive data will be collected on the following variables: demographics, anthropometric information, medical history, laboratory tests, treatment, and AEs. An electronic care report form (eCRF) was developed using the myTrial system^[19]^ of the National Agency for Development of Innovative Technologies in Korean Medicine (IT-KgoM), which supports public eCRFs. Table 1 shows the data collection and follow-up schedules.

**Figure 1 F1:**
[figure not shown]
Study flow chart. BMI = body mass index, BP = blood pressure, KM = Korean medicine.

**Table 1 T1:** Study schedule of the registry study.

	Enrollment baseline	Subsequent visits	End of treatment
Informed consent	V		
Eligibility screening	V		
Demographic characteristics	V		
Body mass index	V		V
Body composition test	V		V
Liver function tests	V		V
Kidney function tests	V		V
Herbal medicine	V	V	V
Blood pressure, body temperature, pulse rate	V		V
Adverse event		V	V

### Study registration

2.2

This study is registered with the Clinical Research Information Service (https://cris.nih.go.kr/cris/en/): KCT0006792. Current protocol versions are 1.2.

### Eligibility criteria

2.3

#### Inclusion criteria

2.3.1

We will include eligible patients according to the following criteria:

(1)Men and women aged between 19 and under 65 years of age.(2)Among the patients who visited the hospital for weight loss, those who decided to undergo HM treatment.(3)Patients who have listened to sufficient explanation before registry registration, agreed to participate in this study voluntarily, and signed written informed consent approved by the institutional review board.

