#### Exclusion criteria

2.3.2

(1)Patients who do not take HM for weight loss.(2)Patients who do not agree to registry registration.(3)Participants who are judged to be inappropriate for participating in this study.

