### Recruitment

2.4

The participants will be recruited from KM obesity clinics of 15 KM primary medical institutions across Korea. The researcher will fully explain the aim of this study and details of the procedures, including research usage, confidentiality, and providing data provision to third parties for analysis and will obtain informed consent from the potential participants who met the inclusion criteria before the collection of information.

Participants will be free to withdraw at any time during the study, and this will not affect their clinical treatment. We encourage voluntary participation in this study by posting recruitment posters on the walls of the entrance and elevators of the each clinic.

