### Outcomes measures

2.6

Researchers determined that the following data will be collected for observing the characteristics of KM weight loss treatment. Detailed research schedule and variables are presented in Table 2.

(1)*Demographics*: Age, sex, and medical history will be collected as basic demographic information.(2)*Anthropometric data*: If a participant visits physically for consultation, vital signs, including blood pressure, body temperature, and pulse rate will be collected as variables related to general health conditions. Weight, height, and body mass index (BMI) will be measured as variables for weight change. Body fat mass, body muscle, visceral fat level, etc will be measured as variables for changes in body composition.(3)*Liver and kidney function tests*: To evaluate the physical changes induced by long-term administration of HM or weight loss, liver function (aspartate aminotransferase, alanine aminotransferease) and renal function tests (blood urea nitrogen, creatinine) will be conducted at the visit.(4)*Other laboratory test*: Total cholesterol, high-density lipoprotein, low-density lipoprotein, triglycerides, etc will be evaluated at the visit to evaluate the physical changes induced by long-term administration of HM for weight loss.(5)*HM treatment*: For the observation and collection of real clinical data, there will be no restriction on the type or frequency of HM treatment, and doctors in the primary KM clinics will perform the HM treatment according to the characteristics of the individuals. For a given period, prescription medication will be recorded with the name of the medicine, medicine composition, and treatment duration.(6)*AEs*: At each treatment visit, participants will be investigated by the KM doctors using the AEs template developed by the expert Delphi group to evaluate the occurrence of any AE. In case of occurrence of any AE, we will immediately provide appropriate treatment to the participant according to the guidelines of the clinic, and then observe the participant's progress during the follow-up visit. The name, severity, and duration of the AEs that occur during the study period will be recorded. In addition, any causality assessments between the AE and the KM treatment will be evaluated by the investigator during visits. All investigators and KM doctors will be educated in research ethics (Table 2).

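### Eligibility and baseline do not separate first-time from returning or recently treated users of weight-loss herbal medicine, so some baselines may not be pre-treatment and adverse-event incidence and before/after change may be biased

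*Protocol article*

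**What the plan says.** The eligibility lists in sections 2.3.1 and 2.3.2 of the protocol article have three inclusions and three exclusions. On HM treatment, the inclusion is "Among the patients who visited the hospital for weight loss, those who decided to undergo HM treatment" and the exclusion is "Patients who do not take HM for weight loss". The remaining items cover age, consent and a discretionary exclusion, "Participants who are judged to be inappropriate for participating in this study". None mentions a first course, an HM-free interval or current use.

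Section 2.1 fixes the time of baseline: "At baseline (recruitment), comprehensive data will be collected on the following variables: demographics, anthropometric information, medical history, laboratory tests, treatment, and AEs". Section 2.6 lists what is collected. Under demographics it says "Age, sex, and medical history will be collected as basic demographic information". Under HM treatment it says "For a given period, prescription medication will be recorded with the name of the medicine, medicine composition, and treatment duration", and also that "there will be no restriction on the type or frequency of HM treatment". No look-back before enrolment is named. Table 1 marks HM at enrolment and at every later stage, and AEs only after enrolment.

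Section 2.9 plans paired tests of values before and after treatment, tests between groups, and analysis of covariance where underlying variables need control, with demographic variables as the example. Earlier HM use is not mentioned. The Introduction gives two aims: to describe patients and current treatment, and to evaluate the safety of the HMs used.

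**The concern.** A before/after comparison is what its name says only if the first measurement precedes treatment. Here the first measurement is tied to enrolment, and nothing in the eligibility criteria ties enrolment to the start of HM. Someone beginning a second or later course has also decided to undergo HM treatment.

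Two mechanisms follow for patients with current or recent exposure:

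- **Selection on tolerance.** Patients who had troublesome AEs on an earlier course are less likely to come back. Those who do come back would tend to show fewer AEs than first-time users, which lowers the pooled incidence.
- **Change before baseline.** Part of the weight loss, and any early shift in liver or kidney tests, may have happened before enrolment. The paired difference then understates the change from an untreated state, and a real laboratory change could be partly hidden.

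The second aim is safety, section 2.6 gives the laboratory tests the purpose of detecting changes from long-term HM or weight loss, and the Discussion says the safety results are to feed clinical practice guidelines. An AE incidence that mixes starters and tolerant returners could be read there as the risk on starting HM, which it would not be.

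**Working it through.** **The plan's own figure.** Section 2.8 plans at least 1000 patients on feasibility grounds. 15 clinics × 65 patients per clinic per year × 1 year = 975, which is 2.5% below 1000. Since the rate is given as a minimum, the figure is consistent (1000 / 15 = 66.7 per clinic). It carries no event rate, standard deviation or assumption about prior HM use, so nothing in it bears on the share of prior users.

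**Mixture model.** Let s be the share of enrolled patients with current or recent weight-loss HM, and r their AE risk relative to new starters. Then

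pooled / new-starter value = (1 − s) + s·r, so the relative bias is −s(1 − r).

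Both s and r are assumptions; the protocol gives neither. The percentage column also assumes a new-starter AE risk of 30%.

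| s | r | Pooled AE incidence | Relative bias |
|---|---|---|---|
| 10% | 0.5 | 28.5% | −5% |
| 30% | 0.5 | 25.5% | −15% |
| 50% | 0.5 | 22.5% | −25% |
| 10% | 0.75 | 29.25% | −2.5% |
| 30% | 0.75 | 27.75% | −7.5% |
| 50% | 0.75 | 26.25% | −12.5% |
| any | 1.0 | 30% | 0 |
| 10% | 1.25 | 30.75% | +2.5% |
| 30% | 1.25 | 32.25% | +7.5% |
| 50% | 1.25 | 33.75% | +12.5% |

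Example: s = 30%, r = 0.5 gives 0.7 × 30% + 0.3 × 15% = 25.5%.

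**Weight change.** The same formula applies with f, the fraction of a new starter's loss still to come after enrolment, in place of r. With an assumed −5 kg in new starters:

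- mildest case, s = 10%, f = 0.75: −5 × (0.9 + 0.1 × 0.75) = −4.875 kg, a shortfall of 2.5%;
- middle case, s = 30%, f = 0.5: −5 × (0.7 + 0.3 × 0.5) = −4.25 kg, a shortfall of 15%;
- most severe case, s = 50%, f = 0.25: −5 × (0.5 + 0.5 × 0.25) = −3.125 kg, a shortfall of 37.5%.

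**Direction.** The bias is downward only if r < 1. The reverse is possible for AEs: section 2.1 lists AEs among the baseline data, but Table 1 marks them only at later visits and at end of treatment. If AEs from an earlier course are not recorded at enrolment, one that persists could be counted as new.

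**Precision after splitting.** The 95% half-width for an incidence of 30% is 1.96 × √(0.3 × 0.7 / n), ignoring clustering by clinic. It is 2.8 percentage points for n = 1000, 3.4 for n = 700 and 4.0 for n = 500.

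**The case against.** The wording leans towards a course that begins at enrolment. Patients have decided to undergo treatment, those who consent will then receive it, and section 2.9 speaks of values before and after treatment. Enrolling someone in mid-course strains that language. A returning patient whose new course starts at enrolment does have a baseline that precedes that course. This narrows the problem but does not remove it: such a patient is still selected for earlier tolerance, and recent HM may still affect weight and laboratory values.

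Earlier HM use may also be recorded already. Medical history, treatment and HM are baseline items, and the Discussion mentions treatment history. The case report form and the full protocol are not shown, so it cannot be claimed that the information is missing. A field alone, however, would not separate the groups in eligibility, in the definition of baseline or in the stated comparisons.

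A mixed population suits a registry of routine practice, and repeat users are informative about long-term administration. That stands for the descriptive aim, and it argues against restricting enrolment or making new starters the only analysis set.

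Three stronger readings are tempting but not supported:

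- A reader might infer that recruitment by "posting recruitment posters on the walls of the entrance and elevators of the each clinic" fills the registry with patients already on treatment. First-time visitors see the same posters, so they say nothing about the share of prior users.
- A reader might infer that section 2.9 commits to pooling everyone. It states no split by prior use, but it provides for group comparisons and covariate adjustment and does not rule one out.
- A reader might infer that the results are biased downward. That requires a material share of prior users and r < 1, and the protocol establishes neither.

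**Conclusion.** The point holds in a limited form. The listed criteria admit returning or recently treated users, baseline is recruitment and not first HM dose, and no split or adjustment by prior use is stated. The enrolment values of such patients may therefore not be pre-treatment values, and AE incidence and before/after change may be biased. Downward is the likelier direction.

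The size cannot be derived from the protocol. For assumed shares of 10% to 50%, pooled AE incidence runs from 25% below the new-starter value (r = 0.5) to 12.5% above it (r = 1.25), and the shortfall in weight loss from 2.5% to 37.5% (f from 0.75 to 0.25). If few patients have prior exposure, or their risk equals that of new starters, the effect is negligible. The point is still worth acting on, because the groups can be separated later only if earlier use and its dates were captured; otherwise they must be rebuilt from recall or charts.

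**What to change.** - At enrolment, record whether the patient is using, or within a fixed look-back window has used, HM for weight loss, with the date of the last dose. If the existing medical history or HM fields already hold this, confirm it and state the window.
- Report AE incidence and before/after changes separately for new starters and for continuing or returning users. Use the new-starter stratum for statements about AE incidence after starting HM and about change from a pre-treatment baseline.
- Keep the whole cohort for the description of patients and current practice. Enrolment, treatment and the planned 1000 do not change.

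The cost is at most one field in the electronic case report form, plus lower precision within each stratum. For example, the half-width on a 30% incidence would widen from 2.8 to 3.4 percentage points if 700 of 1000 patients were new starters, and to 4.0 if 500 were.

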#### Exclusion criteria

2.3.2

(1)Patients who do not take HM for weight loss.(2)Patients who do not agree to registry registration.(3)Participants who are judged to be inappropriate for participating in this study.

### Recruitment

2.4

The participants will be recruited from KM obesity clinics of 15 KM primary medical institutions across Korea. The researcher will fully explain the aim of this study and details of the procedures, including research usage, confidentiality, and providing data provision to third parties for analysis and will obtain informed consent from the potential participants who met the inclusion criteria before the collection of information.

Participants will be free to withdraw at any time during the study, and this will not affect their clinical treatment. We encourage voluntary participation in this study by posting recruitment posters on the walls of the entrance and elevators of the each clinic.

### Exposure

2.5

The purpose of this study is to observe various situations from routine clinical practice, which differs from other clinical trials that evaluate the efficacy of specific interventions.

The participants will receive individualized general HM in KM treatments. There will be no added interventions for this study, and general KM treatments will be administered to the patients in accordance with safety regulations. The KM doctors, who are participating voluntarily, have over 5 years of clinical experience treating patients with obesity.

### Outcomes measures

2.6

Researchers determined that the following data will be collected for observing the characteristics of KM weight loss treatment. Detailed research schedule and variables are presented in Table 2.

(1)*Demographics*: Age, sex, and medical history will be collected as basic demographic information.(2)*Anthropometric data*: If a participant visits physically for consultation, vital signs, including blood pressure, body temperature, and pulse rate will be collected as variables related to general health conditions. Weight, height, and body mass index (BMI) will be measured as variables for weight change. Body fat mass, body muscle, visceral fat level, etc will be measured as variables for changes in body composition.(3)*Liver and kidney function tests*: To evaluate the physical changes induced by long-term administration of HM or weight loss, liver function (aspartate aminotransferase, alanine aminotransferease) and renal function tests (blood urea nitrogen, creatinine) will be conducted at the visit.(4)*Other laboratory test*: Total cholesterol, high-density lipoprotein, low-density lipoprotein, triglycerides, etc will be evaluated at the visit to evaluate the physical changes induced by long-term administration of HM for weight loss.(5)*HM treatment*: For the observation and collection of real clinical data, there will be no restriction on the type or frequency of HM treatment, and doctors in the primary KM clinics will perform the HM treatment according to the characteristics of the individuals. For a given period, prescription medication will be recorded with the name of the medicine, medicine composition, and treatment duration.(6)*AEs*: At each treatment visit, participants will be investigated by the KM doctors using the AEs template developed by the expert Delphi group to evaluate the occurrence of any AE. In case of occurrence of any AE, we will immediately provide appropriate treatment to the participant according to the guidelines of the clinic, and then observe the participant's progress during the follow-up visit. The name, severity, and duration of the AEs that occur during the study period will be recorded. In addition, any causality assessments between the AE and the KM treatment will be evaluated by the investigator during visits. All investigators and KM doctors will be educated in research ethics (Table 2).

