### Statistical analysis

2.9

All statistical analyses will be conducted via two-tailed tests, and the significance level will be set at 5%. Categorical variables will be presented as n (%) whereas continuous variables will be expressed as mean ± standard deviation. For comparison of two or more groups, categorical variables will be subjected to the chi-square test and Fisher's exact test, whereas continuous variables will be analyzed using the *t* test and analysis of variance or non-parametric methods, such as Mann–Whitney *U* test and Kruskal–Wallis test, for those not meeting the normality criteria. Pre- and post-treatment comparison conducted with a paired *t* test or Wilcoxon signed rank test will be analyzed using a Kolmogorov–Smirnov test. Analysis of covariance will be performed when it is necessary to control the underlying variables, such as demographic variables. For data with a missing value, the last observation carried forward will be used through case report form (CRF) inspection to replace the missing value. All statistical analyses in this study will be conducted using SAS software, version 9.4 (SAS Institute, Inc., Cary, NC).

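### Section 2.6(2) makes vital signs depend on physical attendance and Table 1 does not; with two scheduled points, LOCF turns each missing end-of-treatment value into zero change

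*Protocol article*

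**What the plan says.** Three statements in the protocol article bear on this point.

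- **Section 2.6, item (2).** Vital signs carry a condition: "If a participant visits physically for consultation, vital signs, including blood pressure, body temperature, and pulse rate will be collected". The next two sentences carry none: "Weight, height, and body mass index (BMI) will be measured as variables for weight change", and "Body fat mass, body muscle, visceral fat level, etc will be measured as variables for changes in body composition".
- **Table 1.** The row "Blood pressure, body temperature, pulse rate" is marked at baseline and at end of treatment, with no mention of attendance. BMI, body composition, and liver and kidney function tests are marked at the same two points. None of these rows is marked at subsequent visits, where only herbal medicine and adverse events appear.
- **Section 2.9.** The sentence beginning "Pre- and post-treatment comparison conducted with a paired" names the t test or the Wilcoxon signed rank test. For missing data, "the last observation carried forward will be used through case report form (CRF) inspection to replace the missing value". The rule makes no exception by variable or by reason for missingness.

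**The concern.** A condition on physical attendance has a purpose only if some contacts are not physical. Table 1 schedules vital signs at two points. Baseline is the point at which patients who have come to the clinic give written consent, so the condition can matter mainly at end of treatment. Section 2.6 thus allows end-of-treatment vital signs to be absent, while Table 1 shows them as collected for everyone.

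The mismatch matters because of the missing-data rule. With a baseline and one later point, LOCF has only the baseline to carry. Each unmeasured patient enters the paired analysis as someone whose blood pressure, pulse, weight or laboratory value did not move. Safety is the second stated aim of the registry, and the Discussion says the results will feed clinical practice guidelines. For a safety variable, filling with no change errs in the reassuring direction.

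**Working it through.** **Inputs from the document.** At least 1000 patients from 15 clinics at 65 or more per clinic per year (section 2.8); two scheduled measurement points (Table 1); paired tests and LOCF (section 2.9). The document does not state the share of patients without an end measurement, the share of remote contacts, or any expected mean or SD of change.

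**The plan's own figure.** 15 × 65 = 975, and 1000 / 15 = 66.7 per clinic. Since 65 is given as a floor, this agrees with 1000. The figure rests on clinic throughput and makes no allowance for missing end measurements.

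**Step 1: what LOCF carries.** Let m be the share without an end measurement (assumed) and D the mean change in measured patients. Unmeasured patients receive end = baseline, so their change is 0.

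LOCF mean = (1 − m) × D + m × 0 = (1 − m) × D

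- m = 10%: 0.90 D, with 900 of 1000 measured
- m = 30%: 0.70 D, with 700 measured
- m = 50%: 0.50 D, with 500 measured

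**Step 2: against the true mean over all patients.** Let unmeasured patients truly change by r × D (r assumed). The true mean is D × [(1 − m) + m r]. Example with m = 0.3 and r = 0.5: 0.7 + 0.15 = 0.85, so measured pairs give 1/0.85 = 1.176 of the truth and LOCF gives 0.7/0.85 = 0.824.

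| r | m | measured pairs / true | LOCF / true |
|---|---|---|---|
| 0.5 | 10% | 1.053 | 0.947 |
| 0.5 | 30% | 1.176 | 0.824 |
| 0.5 | 50% | 1.333 | 0.667 |
| 1 | 10% | 1.000 | 0.900 |
| 1 | 30% | 1.000 | 0.700 |
| 1 | 50% | 1.000 | 0.500 |
| 1.5 | 10% | 0.952 | 0.857 |
| 1.5 | 30% | 0.870 | 0.609 |
| 1.5 | 50% | 0.800 | 0.400 |

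LOCF understates the mean change whenever r is above 0 and is exact only at r = 0. The relative error is m(1 − r)/[(1 − m) + m r] for measured pairs and −m r/[(1 − m) + m r] for LOCF. The two are equal in size at r = 0.5, and measured pairs are closer above that. Below it, LOCF is closer.

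**Step 3: stated precision.** Assume the SD of change s equals D, set both to 1, and let the unmeasured be a random subset. The LOCF variance is (1 − m)s² + m(1 − m)D². At m = 0.3 this is 0.70 + 0.21 = 0.91, so SD = 0.954 and SE = 0.954/√1000 = 0.0302. Measured pairs give 1/√700 = 0.0378. The LOCF interval is about 20% narrower (0.0302/0.0378 = 0.80), although the filled values add no information.

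**The case against.** The strongest reply is that Table 1 is a grid, and grids often omit conditions given in the text. The condition might also be meant only for remote contacts during treatment. The first part has force: the mismatch alone is a matter of wording. The second fits poorly, because Table 1 schedules no vital signs between baseline and end of treatment. If vital signs were in fact also taken at intermediate visits, LOCF would carry a later value for them and the effect would be smaller; Table 1 does not say so.

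It can also be said that the LOCF problem does not depend on visit mode. That is true: any missing end measurement has the same result. Section 2.6(2) matters because it shows that the plan itself foresees one route to such gaps. LOCF is also sometimes defended as cautious for a benefit such as weight loss. That defence does not carry over to blood pressure, pulse or liver and kidney values.

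A reader might infer more: that weight too is taken only on attendance, that remote patients report their own weight, and that weight loss is therefore overstated. The document does not support this. The condition governs the sentence on vital signs only. That a clinic scale needs attendance is a reasonable inference, but it is not stated. Self-reported weight appears nowhere, and section 2.7 has the doctor check measurement results before entry. Any figure for such a bias would rest on an invented remote share and reporting error, and its direction would oppose the LOCF effect. Nor does section 2.9 treat everyone as measured, since it provides for missing values. Whether the eCRF records visit mode cannot be judged from a condensed article, so its absence here is no finding.

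**Conclusion.** The point holds as a fault in how three stated rules combine: a collection condition in 2.6(2) that Table 1 does not carry, a two-point schedule, and LOCF. Together they assign zero change to every patient without an end measurement and shrink the mean change to (1 − m) of that in measured patients, or 90%, 70% and 50% at assumed m of 10%, 30% and 50%. The shrinkage follows from the schedule and the rule. Its size depends on m, which the document does not give. Whether the result is also too small for the whole cohort depends on r: it is for any r above 0.

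The registry is mainly descriptive and states no primary hypothesis, so this is a change that should be made, not one that undermines the study. The main harm is to the reported size and precision of change, above all for the safety measurements.

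**What to change.** - **Section 2.9.** Do not fill missing end-of-treatment vital signs, weight or BMI, body composition or laboratory values from baseline. Base the main pre/post analysis on patients measured at both points. Report the number without an end measurement and their baseline profile, and add a sensitivity analysis for the missing values, for example over a range of r as above.
- **Table 1 and section 2.6(2).** Reconcile them, so that both say the same about when vital signs are collected, and state whether the condition also applies to weight and body composition.
- **Weight source.** If any weight is not measured in the clinic, flag its source and keep it to a sensitivity analysis.

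The cost is a few sentences and a smaller n in the main pre/post table (700 of 1000 at an assumed m of 30%). Measured pairs may still be a selected group: if unmeasured patients changed half as much, they overstate the overall mean change by 5%, 18% and 33% at m = 10%, 30% and 50%. The baseline profile and the sensitivity analysis are therefore needed alongside the main result.
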